# 1. BACKGROUND AND RATIONALE

## 1.1 Lung cancer

Lung cancer is the leading cause of cancer-related mortality worldwide. The poor survival prognosis is largely due to a diagnosis at an advanced stage. However, early-stage non-small cell lung cancer (NSCLC) can be treated with surgical resection, stereotactic radiotherapy, or chemoradiotherapy with curative intent and, thus, has a more favorable prognosis.

The most important risk factor for lung cancer is tobacco smoking. Smoking is associated with approximately 85% of all lung cancer cases in Europe. Increasing age and cumulative exposure to tobacco smoke are the two most common risk factors for lung cancer. Smoking related duration-specific risks for lung cancer increase steadily but are the most significant beyond 20 years of smoking.

## 1.2 Lung cancer screening

Previous trials have shown that lung cancer stage distribution or prognosis cannot be altered with chest x-ray screening. The National Lung Screening Trial (NLST) has demonstrated that screening among adults at high risk using low-dose computed tomography (LDCT) reduced mortality from lung cancer by 20% as compared to individuals who received a standard chest X-ray. Although, these low-dose CT screening benefits were balanced by a very high frequency of false positives; 96% of the positive findings were false-positive results and 23% of all screening test were false-positive results. A recent European LDCT vs. no screening study (NELSON) has demonstrated similar reduction in lung-cancer mortality (24%). Compared to NLST, NELSON study used volumetric assessment of the lesions and this reduced the false-positive rate dramatically to 56.5%. The most important inclusion criteria for NLST and NELSON trial are presented in the Table 2.

Based on these encouraging results, LDCT has been adopted in the USA. Furthermore, many European countries are evaluating implementation of LDCT to national screening programs or initiating pilots to assess feasibility and costs of LDCT screening. However, this is not the case in Finland and LDCT screening has not been evaluated in the country.

**Table 2. Age and smoking history related inclusion criteria of NLST and NELSON trials**

|                 | NLST                                         | NELSON                                 |
|-----------------|----------------------------------------------|----------------------------------------|
| Age (y)         | 55-74                                        | 50-74                                  |
| Smoking history | 30 ≥ pack-years of cigarette smoking history | Smoked ≥15 cigarettes/d for ≥ 25 years |
|                 | Former smokers: quit smoking ≤ 15 years      | Smoked ≥10 cigarettes/d for ≥ 30 years |

## 1.3 Smoking cessation in relation to lung cancer screening

Smoking cessation is recommended to be incorporated to lung cancer screening programs. LDCT screening has been shown to serve as a "teachable moment" that encourages cessation in the high risk smoking population.

Smoking cessation in addition to lung cancer screening could further reduce lung cancer-related mortality beyond the effects of LDCT screening alone. Furthermore, tobacco-related healthcare costs are not only limited to lung cancer diseases and smoking is an important risk factor for e.g. numerous

other cancers and cardiovascular diseases. Therefore, smoking cessation has an extensive health and economical impact.

## 2. OBJECTIVES

### 2.1 Objectives

#### 2.1.1 Primary Objective

- To determine the efficiency of different smoking cessation methods

#### 2.1.2 Secondary Objectives

- To evaluate efficiency of different smoking cessation methods in reduction of smoking
- To assess the sensitivity and positive predictive value of CT-screening
- To evaluate costs related to CT screening

#### 2.1.3 Exploratory Objectives

- To evaluate specificity of CT-screening
- Lung cancer incidence (stage specific) and survival
- Number of additional CT-scans, PET-CT scans, bronchoscopies, needle biopsies, and their results (positive vs. negative for cancer) initiated based on screening CT-findings
- Percentage of subjects identified through newspaper advertisement and referral from primary care physician or occupational health physician
- Quality of life (QoL)
- Spectrum and grading of ePRO symptoms
- Correlation of ePRO symptoms to CT screen results
- Biomarker analysis of blood such as ctDNA
- AI-based evaluation of LDCT scans

#### 2.1.4 Outcome Measures

##### *Primary outcome measures*

- The percentage of subjects who are actively smoking at 3 months after inclusion between the study arms
- The percentage of subjects who are actively smoking at 6 months after inclusion between the study arms

##### *Secondary outcome measures*

- The percentage of subjects who have reduced the amount of smoked cigarettes/d at 3 and 6 months after inclusion between the study arms
- The magnitude and percentage of reduction in cigarettes consumed/d at 3 and 6 months after inclusion between the study arms
- Sensitivity and positive predictive value of CT-screening in the whole cohort
- Costs related to CT screening including additional investigations per patient per year

##### *Exploratory outcome measures*

- Specificity of CT-screening in the whole cohort
- Lung cancer incidence (stage specific) and survival
- Number of additional CT-scans, PET-CT scans, bronchoscopies, needle biopsies, and their results (positive vs. negative for cancer) initiated based on screening CT-findings

- Percentage of subjects identified through newspaper advertisement and referral from primary care physician or occupational health physician
- Quality of life (QoL)
- Spectrum and grading of ePRO symptoms
- Correlation of ePRO symptoms to CT screen results
- Biomarker analysis of blood such as ctDNA
- AI-based evaluation of LDCT scans

### 3. TRIAL DESIGN

This is a prospective randomized two arm Phase II trial to evaluate efficiency of different smoking cessation methods in subjects undergoing LDCT screening for lung cancer (Figure 1). For each subject, the trial will consist of a screening period (maximum four weeks) and intervention phase (for ~1y +/- 3 months). Survival data will be collected beyond the subject's active participation in the trial. The collection of the survival data of a subject is limited to 3 years from the randomization.

The primary objective of the trial is to assess the percentage of subjects who are actively smoking at 3 and 6 months after randomization.

**Figure 2. Study flow-chart**

[figure not shown]

## 4. ELIGIBILITY

### 4.1 Inclusion and Exclusion Criteria

#### 4.1.1 Inclusion Criteria

1. Able to provide written informed consent
2. Age between 50-74y
5. Sm Smoked  $\geq 15$  cigarettes/day for  $\geq 25$  years or smoked  $\geq 10$  cigarettes/day for  $\geq 30$  years and are active smokers (smoking during the last two weeks)
3. Access to a smartphone (iPhone or Android)

#### 4.1.2 Exclusion Criteria

1. A moderate or bad self-reported health; e.g. unable to climb two flights of stairs
2. Body weight  $\geq 140$  kilogram
3. Current or past melanoma, lung, renal or breast cancer
4. A chest CT examination less than one year before inclusion
5. Has known psychiatric or substance abuse disorders that would interfere with cooperation with the requirements of the trial
6. Subject is unwilling or unable to comply with treatment and trial instructions
7. Any condition that study investigators consider an impediment to safe trial participation

#### 4.1.3 Specific Additional Exclusion Criteria

None

## 5. SCREEN AND CONSENT

### 5.1 Informed Consent

Informed consent is obtained by qualified trial investigators according to the standard practice of study site.

### 5.2 Screening

During the screening period, a subject's eligibility for the trial is determined by evaluation of the exclusion and inclusion criteria. Subjects will undergo a medical history review as part of the screening assessment.

The parameters listed below are collected and recorded into the CRF during the screening period. All procedures must occur within 4 weeks.

- Demographic data (age, race, and sex)
- Inclusion/Exclusion criteria
- Medical history and concomitant medications and interventional procedures
- Smoking history
- QoL with EQ-5D
- Blood sampling for biomarkers

## 6. TRIAL ENTRY

Once the subject has signed informed consent, a subject number will be assigned. After the eligibility check and the enrolment confirmation, any change in the subject eligibility criteria needs to be reported in the CRF and the suitability of the subject to enter the study treatment must be carefully evaluated by the investigator. Once assigned, the subject numbers for any screening failures non-evaluable, or discontinued subjects will not be re-used. Intend-to-treat (ITT) population will be characterized by subject who fulfill the inclusion and exclusion criteria and receive smoking cessation intervention in form of either written material or mobile application.

## 7. EXPERIMENTAL PROCEDURES

### 7.1 Randomization

Eligible individuals with written informed consent are randomized (1:1) with stratification according to pack years (<30py or ≥30py), and age (<65 or ≥65v) to experimental smartphone smoking cessation application or control arm.

### 7.2 Smoking cessation approaches

In the control arm, the subjects will be given standard written materials on smoking cessation. After six months of follow-up, the subjects in the control arm will be offered access to the smoking cessation application.

In the experimental arm, the subjects will be given access to a smartphone smoking cessation application in addition to standard written materials on smoking cessation.

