### Intervention Schedule

The intervention period will initiate from randomization. At the randomization visit, all patients will be given written smoking cessation material and blood samples will be collected for biomarker analysis. The patients randomized to intervention arm will be given access to smartphone-based smoking cessation application with user training. The LDCT will be scheduled preferably within six weeks of randomization. After the LDCT, the patient will be informed of the results by mail. If no further procedures are required,

next LDCT will be scheduled for 1y +/- two months). With intermediate LDCT results, follow-up scan will be ordered at three months. With positive LDCT results, the patient will be referred to pulmonologist. At three and six months (+/- one month) after randomization, patient is called to evaluate whether they are active smokers and if they have quit, what is the date of smoking cessation. After the second round LDCT, the subject is scheduled a study visit in which LDCT results are communicated to the subject. In the case of negative LDCT results, patient enters survival follow-up. With intermediate results, new LDCT will be ordered at 2 or 12 months, and positive results will result in referral to pulmonologist. The survival follow-up period can last up to 3 years from inclusion.

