#### 7.2.1 Smoking status follow-up

The smoking status is verified at the baseline during the study visit (T0)

The smoking status (cessation and reduction in smoking) will be verified by a phone call to the study subject at 3 and 6 months (-/+2 weeks). Furthermore, the smoking status is evaluated during the study visit at 1y (+/- 3mo) (T1).

In the experimental arm, the smoking status information obtained by the study personnel can be verified from the data generated by smoking cessation application.

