| NODULE CATEGORY based on volume
NODCAT I      nodule with benign characteristics, as fat/benign calcifications
NODCAT II      solid nodules with a volume of <50 mm 
pleural-based solid nodules with a minimal diameter of <5 mm
non-solid component partial solid nodule with a mean diameter of <8 mm
non-solid nodules with a mean diameter of <8 mm

NODCAT III      solid nodules with a volume of 50-500 mm 
pleural-based solid nodules with a minimal diameter of 5-10 mm
solid nodule with a non-solid component with a mean diameter of ≥8mm

NODCAT IV      solid nodules with a volume of >500 mm 
pleural-based solid nodule with a minimal diameter of >10 mm
solid component in a partial solid nodule with a volume of >500 mm 

NODULE CATEGORY based on volumedoublingtime (growth)
GROWCAT A      volumedoublingtime >600 dagen
GROWCAT B      volumedoublingtime 400-600 dagen
GROWCAT C      volumedoublingtime <400 dagen
new solid component in previously existing non-solid nodule |                               |                                               |                        |                                                            |                                |                                                             |                                |

At three and six months (+/- one month) after randomization, patient is called to evaluate whether they are active smokers and is they have quitted what is the date of smoking cessation.

The survival follow-up period can last up to 3 years from inclusion

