## 10. Smoking Cessation Application

### 10.1 Cessation Application Description and ePRO questionnaire

Participants randomized to the smoking intervention arm will receive a smartphone application for smoking cessation for six months. The smartphone application will also be offered for use after six months of follow-up for the participants randomized to standard-of-care. The cessation application supports the smokers in cessation process and aids them to retain smoking-free lifestyle. The individuals use the app for goal setting, decision-making, information sharing, and empowerment in smoking cessation and, in overall, managing their health.

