### 17.2 Analysis of Outcome Measures

#### 17.2.1 Primary Outcomes

- The percentage of subjects who are actively smoking at 3 months after inclusion between the study arms
- The percentage of subjects who are actively smoking at 6 months after inclusion between the study arms

Eligible subjects are randomized (1:1) with stratification according to pack years (<30py or ≥30py), and age (<65 or ≥65v) to smartphone based smoking cessation and control arm.

The study is powered (80%) with 155 subjects to detect 15% difference in (75 vs. 90%) in the number of active smokers at three and six months after inclusion with 90% confidence. With the expected dropout rate, the sample size is adjusted to 200.

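### The 6-month call has two conflicting windows, and nothing requires a control subject's 6-month smoking status to be recorded before the app is offered

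*Protocol*

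**What the plan says.** **Offer of the app to controls.** Protocol section 7.2: "After six months of follow-up, the subjects in the control arm will be offered access to the smoking cessation application". Section 10.1: "The smartphone application will also be offered for use after six months of follow-up for the participants randomized to standard-of-care". Neither sentence mentions the 6-month call.

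**Timing of the call.** Section 7.2.1 says that smoking status "will be verified by a phone call to the study subject at 3 and 6 months (-/+2 weeks"). The Intervention Schedule in the summary says: "At three and six months (+/- one month) after randomization, patient is called to evaluate whether they are active smokers". The text below Figure 3 repeats the wider window: "At three and six months (+/- one month) after randomization, patient is called". The T3mo and T6mo columns of Table 1 also carry one month either side.

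**Table 1.** The control-arm row has optional entries at T6mo and T1y, in the same columns as the smoking-status assessments. The row label refers to cessation material, not to the app, and no order within the visit is given.

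**Outcome at stake.** Section 17.2.1 lists as a primary outcome: "The percentage of subjects who are actively smoking at 6 months after inclusion between the study arms". The secondary outcomes on reduction in cigarettes per day are also taken at 6 months.

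**The concern.** A call made late in its window falls after the six-month mark. If access for controls opens at that mark, some controls may already be using the tested intervention, or may have been prompted by the offer to try to quit, when their 6-month status is recorded. That would pull the control arm toward the app arm on a primary outcome.

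The conflicting windows are a problem in their own right. Sites schedule calls from the protocol, so two windows mean that the 6-month outcome is not measured over one defined period. The time origin varies as well: the outcome counts from inclusion, the call from randomisation in the summary and below Figure 3, and the offer from a follow-up period whose start is not defined.

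**Working it through.** **Step 1. Offer against latest permitted call (offer read as calendar time).**

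| Source of call window | Latest 6-month call | Longest possible app access before the call |
|---|---|---|
| Section 7.2.1 | 6 months + 2 weeks | 2 weeks |
| Summary, Table 1, text after Figure 3 | 6 months + 1 month | about 1 month |

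If the offer is instead read as following the 6-month contact, this access is zero. The 3-month call is always before the offer under either window.

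**Step 2. Reproduce the planned sample size.** Section 17.2.1: "The study is powered (80%) with 155 subjects to detect 15% difference in (75 vs. 90%) in the number of active smokers", with 90% confidence. Sidedness is not stated; I take a two-sided 10% level, which uses the same critical value as one-sided 5%. Inputs: control 0.90, app 0.75, difference 0.15, z = 1.645 and 0.842.

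- Unpooled: n per arm = (0.90 × 0.10 + 0.75 × 0.25) × (1.645 + 0.842)² / 0.15² = 0.2775 × 6.183 / 0.0225 = 76.3, so 77 per arm, 154 in total.
- Pooled (mean rate 0.825): n per arm = [1.645 × √(2 × 0.825 × 0.175) + 0.842 × √0.2775]² / 0.15² = 78.3, so 79 per arm, 158 in total.

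The stated 155 lies between the two, so the plan's figure is reproduced under this reading.

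**Step 3. Effect of exposure before the call (illustration).** Let f be the fraction of controls using the app before their 6-month call, and e the share of the 15-point effect they have gained, averaged over those exposed. Then

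control smoking rate = 0.90 − 0.15 × f × e.

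The documents give neither f nor e, so both are assumptions. Power is exact (binomial) for the pooled z-test, 77 in the app arm and 78 controls, two-sided 10%, app arm at 75%.

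| f | e | Control rate | Difference (points) | Power |
|---|---|---|---|---|
| 0 | – | 90.0% | 15.0 | 80.8% |
| 5% | 25% | 89.8% | 14.8 | 79.7% |
| 10% | 25% | 89.6% | 14.6 | 78.6% |
| 25% | 10% | 89.6% | 14.6 | 78.6% |
| 25% | 25% | 89.1% | 14.1 | 75.2% |
| 25% | 50% | 88.1% | 13.1 | 69.0% |

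Example for the last row: 0.15 × 0.25 × 0.50 = 0.019, and 0.90 − 0.019 = 0.881.

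A normal approximation with 77.5 per arm gives 79.6% with no exposure and 68.0% in the last row, so the method matters little.

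**The case against.** The strongest reply is that six months of follow-up naturally means that the 6-month follow-up contact has taken place. Section 7.2.1, directly after the offer in 7.2, is headed as smoking-status follow-up and consists of the 3- and 6-month calls and the 1-year visit. The optional control entries in Table 1 fall in assessment columns. A control with a negative first scan has no other scheduled contact around month 6, so early access would need a separate, unscheduled contact before a late call. This reading is reasonable, and it lowers the likelihood of exposure. But the protocol does not state it, so the gap remains.

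The reply is also right about size. Averaged over everyone exposed, half the planned effect within two weeks to a month of access is a severe assumption. A reader might infer that the 6-month comparison will run at about 69% power; the documents do not support that, because they give no uptake, no share of late calls and no speed of effect. Nor could this exposure produce a false positive, since it acts toward no difference.

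The date of quitting is asked for at the call, so quits after the offer could in part be identified, and a rule for using that date may sit in an analysis plan not seen here. It would not help the cigarettes-per-day outcomes, because a subject who only cuts down has no quit date.

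A reader might also infer that app-arm subjects called late have lost the app, because section 10.1 says they "will receive a smartphone application for smoking cessation for six months". No passage says that access is withdrawn at that point, and Table 1 still marks the app at T6mo.

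**Conclusion.** Two things are established from the text. The windows for the 3- and 6-month calls contradict each other, one place against three. And the protocol does not require the 6-month status of a control to be recorded before the app is offered.

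That controls will in fact use the app before their outcome is taken is not established. It is a possibility the wording leaves open, and it depends on reading the offer as calendar time. A reader might take it as a stated procedure; the documents do not say that.

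If it happens, it affects the 6-month primary outcome and the 6-month reduction outcomes, toward no difference. In the scenarios shown, the cost runs from about 1 point of power (5% exposed, a quarter of the effect) to about 12 points (25% exposed, half the effect), and the smaller losses are the more plausible. The stated sample size does not change. I rate this a cheap improvement: the likely damage is modest, but it falls on a primary outcome, cannot be fully undone once it has occurred, and is prevented by wording alone.

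**What to change.** 1. Reconcile the window for the 3- and 6-month calls to one value, counted from randomisation, in the summary, Table 1, section 7.2.1 and the text after Figure 3. The documents give no basis for preferring either value; the sponsor should choose and apply it throughout.
2. In sections 7.2 and 10.1 and in Table 1, state that the app is offered to a control subject only after that subject's 6-month smoking status has been recorded, or after the call window has closed without contact.

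Cost: a protocol amendment and matching site instructions. Control subjects who are hard to reach would get the app days to weeks later. Sample size and analysis are unchanged.

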#### 7.2.1 Smoking status follow-up

The smoking status is verified at the baseline during the study visit (T0)

The smoking status (cessation and reduction in smoking) will be verified by a phone call to the study subject at 3 and 6 months (-/+2 weeks). Furthermore, the smoking status is evaluated during the study visit at 1y (+/- 3mo) (T1).

In the experimental arm, the smoking status information obtained by the study personnel can be verified from the data generated by smoking cessation application.

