### Eligibility

#### Inclusion Criteria:

1. Able to provide written informed consent
2. Age between 50-74
3. Smoked  $\geq 15$  cigarettes/day for  $\geq 25$  years or smoked  $\geq 10$  cigarettes/day for  $\geq 30$  years and are active smokers (smoking during the last two weeks)
4. Access to a smartphone (iPhone or Android)

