### 10.3 Characterization of Properties

The app includes 1) an analysis of the individuals smoking history, 2) two questionnaires for lung-related symptom data and psychosocial wellbeing, 3) smoking diary to enhance self-reflection, and 5) virtual supportive channel providing evidence-based data on the benefits of smoking cessation.

The app aims to:

- Provide analytical data for the user's smoking behavior based on the background data provided by the user and smoking behavioral analysis done using the software
- Help out in making a personalized smoking cessation plan based on users smoking behavioral profile
- Provide behavioral support for smoking cessation
- Provide information on the health benefits of smoking cessation

- Provide long-term follow-up data on user's health status based on symptoms questionnaires and facial photos
- Provide behavioral support for remaining smoking-free after cessation
- Provide data for further development of the application to enhance its performance in smoking cessation and improve the user experience

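### Section 7.2.1 lets app data verify smoking status in the experimental arm only and does not say whether they may change the recorded primary outcome, so the arm comparison can be biased

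*Protocol*

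**What the plan says.** The two primary outcomes in Protocol section 17.2.1 are "The percentage of subjects who are actively smoking at 3 months after inclusion between the study arms" and "The percentage of subjects who are actively smoking at 6 months after inclusion between the study arms".

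Section 7.2.1 gives the method for everyone: "The smoking status (cessation and reduction in smoking) will be verified by a phone call to the study subject at 3 and 6 months". The text after Figure 3 repeats it without limiting it to an arm: "patient is called to evaluate whether they are active smokers". The Intervention Schedule in the protocol summary says the same, and Table 1 has one smoking-status row and one form per time point, not split by arm.

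Section 7.2.1 then adds a sentence for one arm: "In the experimental arm, the smoking status information obtained by the study personnel can be verified from the data generated by smoking cessation application". No trigger, coverage or rule for disagreement between the two sources follows.

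Sections 7.2 and 10.1 offer the app to control subjects only after six months. Section 10.3 lists among the app's contents a "smoking diary to enhance self-reflection", alongside background data that the user provides.

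**The concern.** A self-reported primary outcome has a second information source in one arm and none in the other, at both primary time points. The wording is permissive, so use of that source is left to study staff, and anyone who consults app data necessarily knows the subject's arm. If a diary entry contradicts a claimed quit and the record is changed, false claims are removed in the app arm while the same claims stand in control. The arm difference would then mix the effect of the app with a difference in measurement. Because section 7.2.1 covers reduction as well as cessation, the secondary outcomes on cigarettes per day are exposed in the same way.

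This is a data-collection rule. If staff overwrite the phone answer during the trial, a later analysis plan may be unable to recover it.

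**Working it through.** **The plan's own figure.** Section 17.2.1 gives 155 subjects for 80% power, 75% against 90% active smokers, 90% confidence, 1:1. Sidedness is not stated; two-sided alpha 0.10 reproduces the figure. With unpooled variance:

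n per arm = (1.645 + 0.842)² × (0.75×0.25 + 0.90×0.10) / 0.15² = 76.25, rounded up to 77, or 154 in total.

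The pooled-variance version gives 79 per arm, 158 in total. Both agree with 155 to within 3%. Power at 77.5 per arm is 79.6%. The sample size is therefore not in question; it supplies the design rates and the 15-point yardstick.

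**Model for the one-arm check.** Let m be the share of true smokers who say by phone that they have quit, taken as equal in both arms, and v the share of those claims corrected from app data, in the app arm only. The protocol gives neither value. The assumed ranges are m = 5–10% and v = 0–100%; v = 0 is the case in which app data never change the record.

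- Observed smoking, control = true rate × (1 − m)
- Observed smoking, app = true rate × (1 − m(1 − v))

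**No true effect (90% in both arms).** The app arm appears worse by 0.90 × m × v.

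| m | v | App observed | Control observed | App looks worse by |
|---|---|---|---|---|
| 5% or 10% | 0 | same as control | 85.5% or 81.0% | 0 points |
| 5% | 50% | 87.75% | 85.5% | 2.25 points |
| 10% | 50% | 85.5% | 81.0% | 4.5 points |
| 10% | 100% | 90.0% | 81.0% | 9.0 points |

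**Design effect true (75% app, 90% control).** Observed difference = 0.15 × (1 − m) − 0.75 × m × v. Power is at 77.5 per arm, two-sided alpha 0.10.

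| m | v | Observed difference | Power |
|---|---|---|---|
| 5% | 0 (phone only) | 14.25 points | 70% |
| 5% | 50% | 12.4 points | 60% |
| 10% | 0 (phone only) | 13.5 points | 61% |
| 10% | 50% | 9.75 points | 41% |
| 10% | 100% | 6.0 points | 23% |

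For m = 10% and v = 50%: control 0.90 × 0.90 = 81.0%; app 0.75 × (1 − 0.10 × 0.50) = 71.25%; difference 9.75 points. With the phone answer alone in both arms: 81.0% − 67.5% = 13.5 points. The one-arm correction accounts for the 3.75 points lost.

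**The case against.** The stated measurement is one phone call for every subject. Nothing says app data replace or override the answer, and a check that leaves the record alone adds no asymmetry. This stands. A reader might infer that the outcome is measured by different rules in the two arms and that the comparison is biased, but the documents support neither as fact.

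A reader might also infer that app data would fill in missed calls and so flatter the app. The sentence concerns information that staff have already obtained, and a missed call leaves nothing to verify. That route is not supported.

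The size is assumed throughout. The upper end needs every false claimant to log smoking in the app while denying it by phone. The diary is the same person's self-report, and nothing makes entries compulsory. This stands too, and is why the range starts at zero.

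The check could also reduce bias. Suppose true smoking is 90% in both arms, with false claims of 10% in the app arm and 5% in control. Phone only gives 81.0% against 85.5%, a spurious 4.5-point benefit. With half the app-arm claims corrected, both arms read 85.5%. This is a fair limit on the equal-rates assumption. It shows that the net direction is unknown, but it does not justify leaving the use of the source to discretion.

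Finally, resolving discordant sources is often left to an analysis plan. That answers how to analyse two separately stored sources, but not whether staff may change the phone answer when recording it.

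**Conclusion.** The point holds as a gap in the protocol's wording. Section 7.2.1 permits a discretionary check of the primary outcome in one arm only and does not say whether that check may change the record. Bias follows only if it does.

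Under the assumed 5–10% false claims, equal by arm, and 0–100% correction in the app arm, the distortion with no true effect is 0 to 9 points against the app. With true rates of 75% and 90%, 10% false claims and half corrected, 13.5 points shrinks to 9.75. Against a design difference of 15 points, the middle and upper parts of that range matter. If false-claim rates differ by arm, size and direction can change.

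**What to change.** State in section 7.2.1 that the answer to the same scripted phone question alone defines smoking status at 3 and 6 months in both arms; that app data may not confirm, change or replace it; and that agreement between app data and phone answer is reported descriptively, or used in a sensitivity analysis, for the experimental arm. Align the call script with this.

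The cost is a wording change. No new data are needed, and the required number stays at about 154–158 evaluable subjects. The downside is that some false quit claims stay uncorrected in the app arm, as they already do in control. The change removes only the asymmetry that the protocol itself allows; misreporting that differs by arm would remain.

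Whether the two-week definition of active smoking in the inclusion criteria should also apply at follow-up is a separate matter and not part of this change.
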